#### 2.7.5. Handling of Missing Data, Non-Compliers, and Outliers

Complete case analysis will be the primary method.Multiple imputation may be used if missing data exceeds 10%.Outliers in platelet function tests will be assessed through visual inspection (boxplots, histograms) and verified against source data. Sensitivity analyses may exclude extreme values.

#### 2.7.6. Predefined Subgroup Analyses

Subgroup analyses will explore variations in platelet function and clinical outcomes by:Diabetes status (yes/no)Age groupRenal functionClopidogrel vs. aspirin resistanceSex (male vs. female)

Interaction terms in regression models will be used to evaluate subgroup effects.

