#### 2.7.4. Primary Endpoint Analysis

The primary objective of this study is to evaluate the association between platelet function test results and clinical outcomes in patients undergoing elective and urgent CABG.

Summary Measures

Platelet function results will be summarized as mean ± standard deviation or median with interquartile range (IQR), depending on data distribution, for:AA channel (aspirin response)ADP channel (clopidogrel response)

Clinical outcomes, including MACCE, bleeding, re-exploration, and transfusion, will be reported as frequencies and proportions.

Method of Analysis

Correlation analysis: Pearson’s correlation for normally distributed data, Spearman’s rank correlation for non-parametric dataLogistic regressionEstimates the odds of postoperative events based on platelet resistance status (resistant vs. non-resistant)Adjusts for potential confounders (age, diabetes, renal function, surgical factors)Hierarchical data structure: Generalized estimating equations (GEE) or mixed-effects models will be used to account for repeated measures of platelet function over time.

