### 3.2. Platelet Function and Clinical Outcomes

Platelet function test results will be analyzed at three timepoints: preoperative baseline, postoperative discharge, and six-week follow-up. The degree of platelet inhibition will be reported as percentage inhibition in response to arachidonic acid and adenosine diphosphate pathways, reflecting aspirin and clopidogrel effectiveness, respectively.

The prevalence of aspirin and clopidogrel resistance in the study population will be determined based on predefined cutoff values from the TEG6s Platelet Mapping system. Differences in platelet responsiveness between groups will be evaluated using repeated measures analysis of variance or non-parametric alternatives, depending on data distribution.

The primary analysis will assess correlations between platelet function test results and major adverse cardiovascular and cerebrovascular events, including myocardial infarction, stroke, cardiovascular death, postoperative bleeding complications, and the need for surgical re-exploration. Univariate correlations will be explored using Pearson or Spearman correlation coefficients, while logistic regression models will estimate the odds ratios for adverse outcomes associated with platelet resistance.

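### The subgroup setting clopidogrel resistance against aspirin resistance is cut from the measurement it is compared on, does not partition the cohort, and cannot interact with the stated binary exposure

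*Protocol article*

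**What the plan says.** All references are to the protocol article. Section 2.7.6 names five predefined subgroups under a single lead-in: "Subgroup analyses will explore variations in platelet function and clinical outcomes by:Diabetes status (yes/no)Age groupRenal functionClopidogrel vs. aspirin resistanceSex (male vs. female". Four are patient characteristics: diabetes, age, renal function and sex. The remaining one sets clopidogrel resistance against aspirin resistance. The section adds: "Interaction terms in regression models will be used to evaluate subgroup effects".

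Three other places determine what this item means:

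- Section 3.2 says that the prevalence of resistance "will be determined based on predefined cutoff values from the TEG6s Platelet Mapping system".
- Section 2.7.4 names the platelet-function variables, "AA channel (aspirin response)ADP channel (clopidogrel response", and gives a logistic model for "the odds of postoperative events based on platelet resistance status (resistant vs. non-resistant".
- Section 4 speaks of resistance to either drug or to both, and Section 2.1.4 lists clopidogrel as given only when prescribed.

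The article does not say where patients resistant to both drugs or to neither belong in this subgroup, or which model term the subgroup interacts with.

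**The concern.** A subgroup variable should be defined separately from the outcome it is compared on, should place each patient in one category, and should vary within levels of the exposure it is to interact with. This item has difficulty on all three counts.

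- It is derived from the AA and ADP values and then compared on platelet function, which is those same values.
- Its two categories are not alternatives, since a patient can be in both or in neither.
- Resistance type exists only among resistant patients, and resistance status is the exposure of the logistic model.

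At stake is one of five predefined subgroup analyses. Its platelet-function result could be read as a finding about the two pathways when it reflects only the cutoff. Its outcome result would depend on coding that the text leaves open.

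**Working it through.** The article gives no figure for this subgroup. Its only sample-size calculation concerns a general comparison of platelet-function measures and does not bear on this point.

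**Inputs from the article.** Target 100 patients and about 20% attrition (Section 2.1.1), so 100 × 0.80 = 80 evaluable. Aspirin resistance up to 38% and clopidogrel resistance up to 40% (Section 1); both are upper values.

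**Assumptions.** Channel values are bivariate normal, resistance is the lower tail, the correlation between channels is 0 to 0.7, and the share taking clopidogrel is 20% to 100%. The article states none of these.

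**1. Do the categories partition the cohort?** With B the percentage resistant to both: aspirin only = 38 − B, clopidogrel only = 40 − B, neither = 100 − 38 − 40 + B. At zero correlation, B = 0.38 × 0.40 = 15.2%.

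| Correlation | Both | Aspirin only | Clopidogrel only | Neither | Exactly one |
|---|---|---|---|---|---|
| 0 | 15.2 | 22.8 | 24.8 | 37.2 | 47.6 |
| 0.3 | 19.7 | 18.3 | 20.3 | 41.7 | 38.6 |
| 0.5 | 23.0 | 15.0 | 17.0 | 45.0 | 32.0 |
| 0.7 | 26.8 | 11.2 | 13.2 | 48.8 | 24.4 |

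The contrast covers about 24 to 48 of 100 patients. These figures take everyone as classifiable on both drugs.

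**2. How large is the built-in difference?** At zero correlation, the AA gap between aspirin-only and clopidogrel-only patients equals the gap between values below and above the AA cutoff: φ(z_p) / [p(1 − p)]. At p = 0.38 this is 0.381 / (0.38 × 0.62) = 1.62 SD. Simulation (2,000 runs, N = 100) also gave 1.62 SD at zero correlation and 1.20 SD at 0.5. No subgroup effect was put into the data.

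Share of runs with Mann–Whitney p < 0.05, aspirin-only against clopidogrel-only:

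| Setting | AA | ADP |
|---|---|---|
| 38% / 40%, all on clopidogrel, N = 80 or 100, correlation 0 or 0.5 | 100% | 100% |
| 10% / 10%, all on clopidogrel, N = 100, correlation 0.3 | 98% | 98% |
| 38% / 40%, half on clopidogrel, N = 100, correlation 0.3 | 100% | 86% |
| Same, 30% on clopidogrel | 100% | 47% |
| Same, 20% on clopidogrel | 100% | 26% |

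Shares are among runs with at least two patients per group. In the last three rows, patients off clopidogrel cannot be classed as clopidogrel-resistant but keep ADP values from the same distribution, which is a simplification.

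**3. Is the interaction estimable?** Let R = 1 if resistant to either drug, G = 1 for clopidogrel type and 0 for aspirin type, A = aspirin resistance and C = clopidogrel resistance.

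- R × G among patients with exactly one resistance: R is always 1, so the columns (1, R, G, RG) become (1, 1, G, G). Rank 2 of 4.
- R × G with non-resistant patients added and coded G = 0: G = 1 implies R = 1, so RG = G. Rank 3 of 4. A type contrast can be fitted, but no interaction distinct from it.
- A × G among patients with exactly one resistance: A = 1 − G and AG = 0. Rank 2 of 4.
- A × C in the whole cohort: rank 4 of 4, estimable. One simulated cohort of 100 at correlation 0.3 had 43 with neither, 18 aspirin only, 21 clopidogrel only and 18 both.
- Continuous AA inhibition × G among patients with exactly one resistance: rank 4 of 4, estimable.

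**The case against.** The strongest reply is that a condensed article leaves coding to a fuller document, that the lead-in serves five items and need not pair each with both outcomes, and that the analysis is exploratory. Testing is also done at three timepoints (Section 2.5.1): resistance classified at one and function measured at another is not a comparison of a value with itself. Nor is AA function compared by clopidogrel-resistance status alone.

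Much of this stands, and it limits the point. Four stronger readings are tempting and are not supported:

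- **That the platelet-function contrast must be significant.** The difference is built in; significance depends on numbers. On ADP it fell to 26% of runs when 20% took clopidogrel.
- **That the interaction cannot be estimated at all.** This holds for the binary exposure of Section 2.7.4. Section 2.7.6 does not fix the coding, and other codings are full rank.
- **That the whole item is circular, so the pathway question goes unanswered.** Comparing clinical outcomes by resistance type is not circular and bears on that question.
- **That prescribed regimen would be a subgroup independent of the test.** Section 2.1.2 withholds results from the treating surgical team, Section 6 says they go to the clinical team, who may change treatment, and Section 2.7.8 examines whether resistance influences DAPT use.

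The reply does not remove the core. The choice of subgroup, its listed outcomes and the use of interaction terms are all in the text. Nor does exploratory status fully protect the reader: Section 2.7.9 puts the emphasis on effect sizes and confidence intervals, and in the same-channel comparison the effect size is itself the artefact.

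**Conclusion.** The point holds in limited form. Any same-channel, same-timepoint platelet-function difference in this subgroup is produced by the cutoff. On AA it is about 1.2 to 1.6 SD, under normality, the cited upper rates and correlations of 0.5 down to 0. The two categories overlap and leave out non-resistant patients, so about 24 to 48 of 100 patients fall in exactly one (correlations 0.7 down to 0). With the one exposure that Section 2.7.4 names for the logistic model, the interaction with resistance type is aliased. The overlap and the aliasing follow from the definitions; the numerical sizes rest on the assumptions. Severity is modest, because the analysis is exploratory and the primary analysis does not depend on it.

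**What to change.** Replace the item in Section 2.7.6 with two terms entered together in the clinical-outcome model, in one of two forms:

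- aspirin resistance yes/no and clopidogrel resistance yes/no; or
- standardised AA % inhibition and standardised ADP % inhibition.

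Interpret the clopidogrel or ADP term among patients taking clopidogrel. Report both coefficients and their difference, each with a 95% CI. Patients resistant to both or to neither then have a defined place, and which pathway carries the risk is addressed directly. State that platelet function is not an outcome for this item.

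The data are already being collected, so the change is to the wording and the model specification. The price is one more model term, and a pathway comparison that rests on patients taking both drugs, a share of the 100 that the article does not give.

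Prescribed regimen should not be offered as a test-independent substitute unless Sections 2.1.2 and 6 are reconciled on who sees the results.

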#### 2.1.1. Overall Design

The study will be conducted at a single tertiary NHS cardiac surgery centre, enrolling 100 patients who will receive standard perioperative and postoperative care according to institutional and national guidelines. No study drug or investigational device will be tested. The study aims to generate real-world data that may inform future interventional trials or guideline updates regarding the role of PFT in optimizing antiplatelet therapy for surgical patients.

A formal sample size calculation was performed to ensure sufficient statistical power to detect meaningful variability in platelet function and its association with clinical outcomes. Assuming a moderate effect size (Cohen’s d = 0.5), a two-sided alpha level of 0.05, and 80% statistical power, the minimum required sample size for comparison of platelet function measures was estimated at 63 patients.

To account for an anticipated attrition rate of approximately 20%, due to loss to follow-up or incomplete PFT across multiple perioperative timepoints, the adjusted minimum sample size was calculated to be approximately 80 patients. To further enhance robustness and allow for exploratory subgroup and longitudinal analyses, a final target sample size of 100 patients was selected.

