### 2.7. Statistical Analysis

#### 2.7.1. Baseline Characteristics and Study Flow

Baseline characteristics will be assessed to ensure comparability across participant groups. The following variables will be evaluated:Demographics: Age (continuous), sex (categorical), ethnicity (categorical), BMI (continuous)Clinical history: Diabetes status (categorical), renal function (eGFR, continuous), hypertension (categorical), previous PCI or MI (categorical)Operative details: On-pump vs. off-pump surgery (categorical), number of grafts (continuous), use of antiplatelet agents (categorical)

Continuous variables will be reported as means with standard deviations or medians with interquartile ranges, depending on data distribution. Categorical variables will be presented as frequencies and percentages. Group differences will be assessed using appropriate statistical tests:Student’s *t*-test or Mann–Whitney U test for continuous variablesChi-square or Fisher’s exact test for categorical variables

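### Section 2.7.6 points to an age interaction tested on age groups although age is recorded as continuous; if so, power is lost for no gain (minor)

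*Protocol article*

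**What the plan says.** Section 2.7.6 of the protocol article sets out exploratory subgroup analyses of platelet function and clinical outcomes. The listed factors are "Diabetes status (yes/no)Age groupRenal functionClopidogrel vs. aspirin resistanceSex (male vs. female". Age therefore appears as a grouped factor, while renal function is named without reference to groups. The method sentence that follows reads "Interaction terms in regression models will be used to evaluate subgroup effects".

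Section 2.7.1 gives the scale on which the data are held: "Demographics: Age (continuous), sex (categorical), ethnicity (categorical), BMI (continuous". The same section records renal function as eGFR on a continuous scale.

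Age is also used in two other places. In 2.7.4 it is an adjustment variable in the logistic model for postoperative events. In 2.7.8 it is a candidate predictor in linear regression of % inhibition. Neither is a test of whether age modifies an association.

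**The concern.** Read together, the subgroup list and the method sentence suggest that the product term for age is built from age groups. The study already holds age in finer form, so grouping discards information without saving any data collection. If the true modification changes gradually with age, the grouped test is less likely to find it and the estimated interaction is less precise.

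This matters somewhat more in a study of this size. The sample size in 2.1.1 is set for a main comparison of platelet function measures, not for interactions, and an interaction test generally has less power than a main comparison of the same size. A choice that cuts an already modest power by a quarter or more is worth avoiding when avoiding it is free.

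**Working it through.** **Inputs from the protocol article.** Age continuous (2.7.1). Age group as a subgroup factor, tested through interaction terms (2.7.6). "a two-sided alpha level of 0.05, and 80% statistical power" (2.1.1). "a final target sample size of 100 patients was selected", with "an anticipated attrition rate of approximately 20" percent (2.1.1), so about 80 analysable patients.

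**Inputs assumed, because the article gives none.** Approximately normal age, an interaction linear in age, the number and position of the groups, and the size of the interaction.

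**The plan's own figure.** No power is stated for any subgroup or interaction test. The only power statement is for a main comparison at d = 0.5: "the minimum required sample size for comparison of platelet function measures was estimated at 63 patients". The two-sample formula gives 2 × (1.96 + 0.84)² / 0.5² ≈ 63, which is a number per group. Dividing by 0.8 gives 79, matching the article's figure of about 80. That the 63 is a per-group number is a separate matter. Here it shows only that the sizing does not address interactions.

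**Step 1: information kept by grouping.** For standardised normal age cut into groups with proportions p_k and group means m_k, the share of information kept is Σ p_k m_k².
- Median split: m = ±√(2/π) = ±0.798, so the share is 2/π = 0.637. This is equivalent to using about 64 of 100 patients, or 51 of 80.
- Tertiles: the outer means are ±1.091 and the middle mean is 0, so the share is (2/3) × 1.091² = 0.793.
- Quartiles: 0.861. A 70/30 split: 0.576. An 80/20 split: 0.490.

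**Step 2: effect on power.** If λ is the noncentrality of the continuous-age test, power is Φ(λ − 1.96) + Φ(−λ − 1.96). A two-group split, or an ordered trend score, replaces λ by λ√(share). Unordered groups use a noncentral chi-square on (number of groups − 1) degrees of freedom.

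Example: 35% power on continuous age means λ = 1.96 − 0.385 = 1.575. With a median split, λ = 1.575 × 0.798 = 1.257, and power is Φ(−0.703) ≈ 0.24. In the same way, 59% falls to about 42%.

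| Continuous age | Median split (loss) | Tertiles, 2 df (loss) | Tertile trend (loss) | Quartile trend (loss) |
|---|---|---|---|---|
| 15% | 11.3% (25%) | 10.3% (31%) | 12.9% (14%) | 13.6% (10%) |
| 20% | 14.4% (28%) | 13.1% (34%) | 16.8% (16%) | 17.9% (11%) |
| 30% | 20.8% (31%) | 19.1% (36%) | 24.8% (17%) | 26.5% (12%) |
| 40% | 27.5% (31%) | 25.5% (36%) | 33.0% (17%) | 35.3% (12%) |
| 50% | 34.6% (31%) | 32.6% (35%) | 41.5% (17%) | 44.4% (11%) |

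Losses are relative. Unordered tertiles keep more information than a median split but spend it over two degrees of freedom. Uneven splits cost more: 29–37% at 70/30 and 35–44% at 80/20.

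**Step 3: check by simulation.** In a linear model with 38% of patients resistant (the upper figure for aspirin in the Introduction) and an assumed interaction of 0.2–0.6 SD per SD of age, the median split lost 28–36% of power at N = 80 and 20–33% at N = 100. At N = 100 with an interaction of 0.3, power was 28% on continuous age, 19% with a median split and 18% with tertiles.

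In a logistic model with an assumed 25% baseline event rate, the median split lost 33–38%; at N = 100, for example, 26% fell to 17% and 52% to 34%. At an assumed 10% rate, 24–41% of the grouped models failed to converge. The 70–82% losses seen there are a sparse-data problem, not a measure of the information lost by grouping, and are not used.

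**The case against.** The strongest reply is that 2.7.6 never says how age enters the product term. Listing age group as a factor and using interaction terms are two separate statements. Presenting estimates by age group while testing continuous age would fit both. The article is also a condensed document, and coding details may sit in a full protocol or analysis plan that is not shown. This stands to the extent that the point must be conditional. It does not remove it: grouped testing is the natural reading, and cut-points supplied elsewhere would not recover information lost by testing on groups.

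It is also fair that the size of the loss rests on assumptions. It is smaller with an ordered trend, larger with uneven cuts, and absent if the modification really is a step at the cut.

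Finally, these analyses are exploratory. Section 2.7.9 makes no multiplicity adjustment and puts the emphasis on effect sizes and confidence intervals, and a null interaction would be uninformative at 24% or at 35% power. That limits the weight. It does not favour grouping, which makes the interval for the interaction less precise as well.

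A reader might infer more than the article supports:
- **Missing cut-points as a defect.** A condensed article may leave these to fuller documents.
- **Renal function will be cut.** Section 2.7.6 does not say so, and 2.7.1 records eGFR as continuous.
- **Residual confounding by age.** Section 2.7.4 adjusts the outcome model for age and states no grouping there, and naming an age subgroup does not replace that adjustment.
- **Loss calculated from d = 0.5.** That effect size is for a comparison of platelet function measures. Applied to an age split, it would describe a main effect of age, not effect modification.

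**Conclusion.** The point holds in conditional form and is minor. If the age interaction is tested on groups, if age is roughly normal, and if the modification is roughly linear, a median split costs about 25–31% of the power over a starting range of 15–50%. Unordered tertiles cost about 31–36%, and ordered trends over three or four groups about 10–17%. None of these is a property of the plan as written, since the article fixes neither the number of groups nor their position. It would be wrong to read any single percentage as the loss this study will suffer. No primary conclusion depends on the choice.

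**What to change.** Add to 2.7.6 that effect modification by age will be tested with age as a continuous variable, and that age groups will be used only to display estimates. Add that, if renal function is tested as a modifier, eGFR will stay continuous as recorded in 2.7.1.

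The cost is a sentence or two, with no new data or patients. The test then assumes an approximately linear interaction. The grouped display gives a rough check of that, though with 80–100 patients and possibly few events it will reveal only gross departures.

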#### 2.7.7. Intention-to-Treat Statement

Since this is a non-randomized observational study, an intention-to-treat analysis is not applicable. Analyses will be conducted on participants with complete platelet function and outcome data.

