#### 2.7.3. Handling of Missing Data

Primary analyses will follow a complete case approach. If more than 10% of data is missing for a key variable, multiple imputation may be considered. All missing data patterns will be documented, and deviations will be reported in the final analysis.

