#### 2.7.8. Secondary Endpoint Analysis

Analyses of secondary endpoints are exploratory and hypothesis-generating, as the study is not powered for statistical significance in these measures. Findings will guide future studies.

Variability in Platelet Function

Objective: Assess inter-individual variability in platelet inhibition across timepoints.Analysis:
Continuous values (% inhibition) summarized at baseline, discharge, and 6 weeksRepeated measures ANOVA or Friedman test for within-patient changesBoxplots and line graphs used for visualization

Prevalence of Platelet Resistance

Objective: Determine the proportion of patients with inadequate platelet inhibition.Analysis:
Categorical resistance status reported for each timepoint with 95% confidence intervalsChanges in resistance status analyzed using McNemar’s test for paired categorical data

Demographic and Clinical Predictors of Platelet Function

Objective: Explore associations between patient characteristics and platelet responsiveness.Analysis:
Univariable and multivariable linear regression for continuous % inhibition outcomesConsidered variables: age, sex, BMI, renal function, diabetes, and number of graftsSelection guided by clinical relevance and statistical significance (*p* < 0.1)

Impact of Platelet Resistance on Clinical Decision-Making

Objective: Evaluate whether platelet resistance influences treatment decisions, including DAPT use and discharge timing.Analysis:
Comparisons of DAPT prescription rates between resistant and non-resistant patients using chi-square or Fisher’s exact testLogistic regression to explore predictors of treatment decisions if data allows

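### The complete-data rule in section 2.7.7 makes entry to the primary analysis depend on surviving, and being well enough, to take the six-week platelet test

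*Protocol article*

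**What the plan says.** Section 2.7.7 sets the analysis population: "Analyses will be conducted on participants with complete platelet function and outcome data". It does not limit this to one test or one analysis. Section 2.7.3 adds "Primary analyses will follow a complete case approach", and section 2.7.5 repeats that choice.

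Imputation is optional in both places. Section 2.7.3 says "If more than 10% of data is missing for a key variable, multiple imputation may be considered". Section 2.7.5 sets the same 10% level for missing data in general, without tying it to a variable.

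Section 2.5.1 schedules three tests: before surgery, at discharge (day five to seven, or earlier if the patient leaves earlier), and at six weeks. The Introduction defines MACCE as myocardial infarction, non-fatal stroke and cardiovascular death, assessed at 30 days and one year. Section 2.1.1 allows for "an anticipated attrition rate of approximately 20%, due to loss to follow-up or incomplete PFT across multiple perioperative timepoints".

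For the secondary trend in % inhibition, section 2.7.8 names repeated "measures ANOVA or Friedman test for within-patient" changes. Section 2.7.4 names GEE or mixed-effects models for the repeated measures. No section says how a patient who dies, or is too ill, before a scheduled test is to be analysed.

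**The concern.** The 30-day outcome window closes before the six-week test is due. If a complete series means all three tests, entry to the 30-day analysis depends on a measurement taken after the outcome is known. A patient with a fatal early event can never qualify. One with a disabling stroke or a long intensive care stay may not. Bleeding and re-exploration, also named in the primary objective, can likewise precede the later tests.

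The exclusion is avoidable. Under section 2.5.3 outcomes come from a telephone contact at 30 days and from digital records at 12 months, so they can be known for patients who never attend at six weeks. Most of these patients would also have a usable baseline test. In a cohort of 100, losing even a few events matters for a logistic model of MACCE.

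**Working it through.** **1. The plan's own attrition figure.** Section 2.1.1 goes from 63 to about 80 patients. With 20% loss, 63 / (1 − 0.20) = 78.75, rounded up to 79, so this step reproduces. It treats a patient with an incomplete test series as lost, which supports the three-test reading of section 2.7.7.

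**2. The 20% against the 10% level.**
- Per patient: 20% of 100 is 20 incomplete patients, against a level of more than 10. If each patient has a 20% chance of being incomplete, the binomial probability of more than 10 in 100 is 0.994.
- Per variable (the wording of section 2.7.3), if all incompleteness comes from the three tests: gaps that never overlap give 0.20 / 3 = 6.7% missing per test. Independent gaps give 1 − 0.80^(1/3) = 7.2%. If the loss is all dropout or death, the six-week test can reach 20%.

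The 10% level is therefore passed under section 2.7.5, but under section 2.7.3 only if losses concentrate.

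**3. Effect on the primary association.** The inputs are assumptions. The documents give no event rates, and 38% is the upper figure the Introduction quotes for aspirin resistance.
- 100 patients, 38 resistant and 62 not.
- MACCE risk 10% in non-resistant patients: 6.2 events, 55.8 non-events.
- True odds ratio 2.0: odds in resistant patients 2 × 0.10/0.90 = 0.222, risk 18.2%, so 6.9 events and 31.1 non-events. Total about 13.1 events.
- In non-resistant patients half the events fall before six weeks: 3.1 early, 3.1 late.
- All non-event patients are kept.

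Scenario A, same early share in both groups: resistant 3.45 early, 3.45 late.
Scenario B, all the excess is early: resistant late events 38 × 5% = 1.9, early events 5.0.

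| Scenario | Early-event patients lost | Resistant events left | Non-resistant events left | Total events | Risks observed | Odds ratio |
|---|---|---|---|---|---|---|
| None lost | 0% | 6.9 | 6.2 | 13.1 | 18.2%, 10.0% | 2.0 |
| A | 60% | 4.84 | 4.34 | 9.2 | 13.5%, 7.2% | (4.84/31.1)/(4.34/55.8) = 2.0 |
| A | 100% | 3.45 | 3.10 | 6.6 | 10.0%, 5.3% | (3.45/31.1)/(3.10/55.8) = 2.0 |
| B | 60% | 3.90 | 4.34 | 8.2 | 11.2%, 7.2% | (3.90/31.1)/(4.34/55.8) = 1.61 |
| B | 100% | 1.90 | 3.10 | 5.0 | 5.8%, 5.3% | (1.90/31.1)/(3.10/55.8) = 1.10 |

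Events and absolute risks fall in every row with loss. The odds ratio changes only in scenario B, where a larger share of events is lost among resistant patients.

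**4. A second set of assumed risks.** With 15% and 5%, the true odds ratio is 3.35. If 25% or 50% of events are lost in the resistant group only, it becomes 2.51 or 1.68. If 50% are lost in both groups it stays at 3.35, while the risks fall to 8.1% and 2.6%.

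**The case against.** The strongest defence is that the article never defines complete. Section 2.7.2 counts test completion at each timepoint separately from the number in endpoint analyses. Section 2.7.8 reports resistance by timepoint, and the GEE or mixed models of section 2.7.4 can use partial series. The authors may intend analysis-specific sets, in which case a baseline-only analysis would keep early deaths. That is possible, but section 2.7.7 contains no such limit and section 2.1.1 counts incomplete series as attrition. The sentence needs correcting on either reading.

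Three stronger readings are tempting, and the documents do not support them.
- A reader might infer that the odds ratio must be pulled towards 1. It need not be: scenario A leaves it unchanged, and the fall in scenario B follows from placing all the excess risk early. Only death before six weeks necessarily prevents the third test, so the rows with every early-event patient lost are extremes.
- A reader might infer that the plan already breaches its own imputation rule. Imputation is only permitted, never required, and the 20% is per patient while section 2.7.3 counts per key variable.
- A reader might infer that the 20% reflects deaths and severe illness. Section 2.1.1 names only loss to follow-up and incomplete testing. The illustration loses about 4 to 8 patients, all with events, and should not be equated with the 20.

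The analysis of variance or Friedman choice affects only a secondary analysis that the plan calls exploratory. It is a minor part of the point.

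**Conclusion.** The point stands in this form. As worded, section 2.7.7 with the complete-case rule excludes any patient who dies before the six-week test, and may exclude those too ill for it, so inclusion in the primary analysis depends on the outcome. This rests on reading complete as all three tests, which is the plain reading but is not spelled out.

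The consequence that does not depend on differential loss is understated early events and absolute risks: in the illustration, from about 13 events to between 5 and 9. Bias in the odds ratio is conditional. From a true value of 2.0 it ranges from none (equal proportional loss) to 1.6 or 1.1 (all excess early, with 60% or all of the early-event patients lost). Event rates, timing and loss fractions are assumptions.

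On missing data, complete case is fixed as primary although the expected per-patient incompleteness is twice the level at which section 2.7.5 would allow imputation. Per test, missingness could be about 7%, or as high as 20% at six weeks. Imputation alone would not cure the main fault, because a platelet value after death has no meaning.

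**What to change.** Replace the sentence in section 2.7.7 with wording such as: *Each outcome analysis names the platelet function test that serves as its exposure and counts only events after that test. It includes every patient who had surgery and has that test. Missing later tests do not exclude a patient.* For example, use the baseline test for outcomes from surgery onward, and the discharge test only for events after it. Naming the test is essential: if a later test is the exposure and earlier events are still counted, the survivor selection remains.

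In sections 2.7.3 and 2.7.5, use one definition of the 10% level. State that platelet function is not imputed after death. Where missingness in covariates, or in the exposure test among living patients, exceeds 10%, report multiple imputation alongside complete case.

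For the secondary % inhibition trend, use a mixed model with time as a factor on all available tests, a model type section 2.7.4 already names, in place of repeated measures analysis of variance or Friedman. These discard any patient missing one of the three tests.

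The cost is wording and a little programming, with no new data. Analyses based on the discharge test will have fewer events, because earlier ones are not counted, and they describe only patients who reach that test.
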